#### Timelines

The study started in November 2017, and the recruitment phase will last until April 2019.

There will be three follow-up examinations after 2, 6, and 12 months, with the last planned for April 2020. We plan to complete the evaluations and cost analyses by December 2020.

From the patient’s perspective, the study will start with a preadmission screening (T0, at most 3 weeks before admission) (see Fig. 3). Admission (T1) will be followed by surgery and then daily delirium screening for 7 days (T2–T8) during hospitalization. A final discharge assessment (T9) will take place 1–8 days after surgery. If, at this point, the patient is considered to suffer from delirium, then delirium screening and monitoring will continue for another 2 weeks, so long as the patient remains hospitalized in the center. The discharge examination (T9) will take place, at the latest, 3 weeks after the elective surgery, with the participation of a physician who will note any postoperative complications. Follow-up assessments will be performed after 2 months (T10), 6 months (T11), and 12 months (T12). Moreover, the patient’s relatives will be asked at T12 about their care burden using the G-ZBI, and the cognitive state of the patient will be assessed using the IQCODE instrument. If a patient is unable or unwilling to go to the regional center for any follow-up assessment, the local PAWEL team will offer the assessment either at some hospital closer to the patient or at the patient’s general physician’s practice. If the patient is not able to go to any of these places, a team member will assess the patient at the patient’s home. Finally, if the patient refuses this option, he or she will be asked for a telephone interview.

#### Sample size

The power analysis for the primary outcome of delirium prevalence assumes a reduction in the outcome from 25% to 15% [20] as a result of the intervention. A conventional analysis to detect differences in proportions (delirium rate) between the intervention and control groups, using Fisher’s exact test, results in a total of 514 patients with a 1:1 randomization, given a power of 1 – β = 0.80 and an α error of 5%. Using the adjustment form proposed by Woertman et al. [67] with five crosspoints in a stepped-wedge design, with a maximum of 50 patients per cluster per period and an intracluster correlation of 0.01, leads to a correction factor for the stepped-wedge design of KF = 2.63, and therefore a number of 514 × 2.63 = 1351 patients. Assuming a dropout rate of 15%, this leads to a total requirement for about 750 patients per arm. The minimum number of clusters is given by the ratio of the total number of patients to the product between the number of crossing points and the patients per cluster per period, and is 15.

For the secondary outcomes, a reduction of the persistent cognitive deficit from 20% to 10% results in 428 patients using the conventional analysis with Fisher’s exact test and a 1:1 randomization, a power of 1 – β = 0.80, and an α error of 5%, which after the design correction leads to a requirement of 1079 patients.

Thus, the planned sample size is of at most 1500 patients (see Fig. 1 with the numbers per period). Furthermore, relatives of the patients will be asked about the burden of caring and the cognitive status of the patients.

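### The planned 1500 patients do not contain the stated 15% dropout allowance: 1351 / 0.85 is 1590, so 1500 covers only about 10% loss

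*Protocol article*

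**What the plan says.** The Sample size section builds the primary-outcome figure in four steps.

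1. For a fall in delirium from 25% to 15%, a comparison of two proportions "using Fisher’s exact test, results in a total of 514 patients with a 1:1 randomization", "given a power of 1 – β = 0.80" and a 5% alpha error.
2. A stepped-wedge correction factor of 2.63 is applied. It is based on five crossing points, a maximum of 50 patients per cluster and period, and an intracluster correlation of 0.01. The product is given as 1351.
3. Dropout is then added: "Assuming a dropout rate of 15%, this leads to a total requirement for about 750 patients per arm".
4. After the secondary-outcome calculation, which starts from 428 patients for 20% versus 10%, the section concludes: "Thus, the planned sample size is of at most 1500 patients".

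The abstract and the Design section also give 1500. The registration table lists 1800 for the delirium risk score, but says that 1500 of these serve the comparison of the intervention.

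**The concern.** Step 3 presents 750 per arm as the result of adding a 15% allowance to 1351, and 1500 is too small to be that result. Because step 4 makes 1500 a ceiling, the gap cannot be closed by enrolling a little more under the plan as written.

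This section is the only justification of size for the primary outcome. If the stated dropout occurs, the trial has less than the 80% power it claims, and a null result would be read against a power it did not have. The starting figure of 514 also looks low for the test that the plan names, and that error runs in the same direction.

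**Working it through.** **Inputs, all from the Sample size section:** 25% versus 15%; Fisher's exact test; power 0.80; alpha 5%; 1:1 allocation; 514 before correction; factor 2.63; 1351 after correction; dropout 15%; about 750 per arm; maximum 1500. The section does not say whether alpha is one- or two-sided. Two-sided is assumed here, and the check on 428 below supports that.

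**Reproducing the plan's product.** 514 × 2.63 = 1351.8, which the plan gives as 1351. This step is sound.

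**Dropout step.** Enrolled = evaluable / (1 − dropout).
- 1351 / 0.85 = 1589.4, so 1590 enrolled (795 per arm).
- The cruder inflation, 1351 × 1.15, gives 1554.
- The plan's 1500 is 90 below the first figure and 54 below the second. Neither convention yields it.

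**What 1500 does cover.**
- Dropout allowed on the plan's own 1351: 1 − 1351/1500 = 9.9%.
- Evaluable at 15% dropout: 1500 × 0.85 = 1275, which is 76 short of 1351.

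**Power with 1275 evaluable.** The plan's factor is used to return to the individually randomized scale: 1275 / 2.63 = 484.8, so 242 per arm.
- Exact two-sided Fisher power, 25% versus 15%: 75.6%.
- Normal approximation without continuity correction: 78.7%.
- For comparison, with no loss at all: 1500 / 2.63 = 570.3, so 285 per arm, with 82.7% Fisher power.

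**The starting figure of 514.** Exact two-sided Fisher power was computed by enumeration.

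| Comparison | Total | Power |
|---|---|---|
| 25% vs 15% | 514 (plan) | 78.2% |
| 25% vs 15% | 532 | 79.9% |
| 25% vs 15% | 534 | 80.1% |
| 20% vs 10% | 426 | 79.9% |
| 20% vs 10% | 428 (plan) | 80.1% |

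The named test therefore needs 534 for the primary outcome. The same method returns the plan's 428 for the secondary outcome exactly, so 514 is out of line with the plan's own method. For 25% versus 15%, the normal-approximation formula gives 500 without and 540 with continuity correction, so neither explains 514.

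**Both corrections together, keeping 2.63.** 534 × 2.63 = 1404. Dropout allowed by 1500: 1 − 1404/1500 = 6.4%.

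**The case against.** The strongest reply is that the shortfall is modest and conditional. On the plan's 1351, the target is met if no more than about 10% are lost. With no loss, Fisher power is about 83%. Even at 15% loss the normal approximation is within two points of 80%. Fisher's test is also only a starting approximation, since the Statistical analysis section plans logistic regression with cluster adjustment. All of this stands. It limits the size of the problem but does not make the dropout sentence correct: the section itself applies 15% to the primary outcome, and no other section repairs the sum. The 1800 in the registration table does not help, because that table assigns only 1500 to the comparison.

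Three stronger readings are not supported.

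- *A reader might infer that the factor 2.63 is also wrong and should be 2.70.* The usual form of the adjustment gives 2.70 at 50 per cluster-period and 2.63 at 40, if one baseline period is assumed. With two baseline periods it gives 3.00 at 50. The section does not state the number of baseline periods, and it calls 50 a maximum, not the value used. The factor is therefore not shown to be wrong, and no corrected total or power should be built on another value.
- *A reader might infer that the trial simply lacks 80% power.* That holds only if loss reaches the stated 15%, or exceeds the smaller allowance that 1500 does contain.
- *A reader might dismiss the 15% because delirium is measured in hospital.* The Outcome assessment section adds assessments at 2 and 6 months to the 7-day screening, so the primary outcome is not purely in-hospital as defined. The Withdrawal section also lists reasons that can arise within the first week, such as death and longer reoperation. Loss for the 7-day assessment may well be lower, but the article gives no separate rate.

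**Conclusion.** The dropout step is wrong as written. At 15% loss the plan's own 1351 calls for 1590 enrolled, while 1500 covers about 10%. If 15% are lost, power is about 76% on the plan's Fisher scale (about 79% by normal approximation), against a stated 80%. The 514 is a smaller, secondary error: 534 is needed, and 514 gives 78.2%.

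These figures rest on a two-sided 5% alpha, the plan's rates of 25% and 15%, and its factor of 2.63 taken as given. The error does not invalidate the design or require a larger trial. It means that the stated size, dropout and power cannot all hold together, and the text should be corrected before the power claim is relied on.

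**What to change.** Keep 1500 and make the text agree with it, in one of these ways.

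- **Restate the power.** For example: *1500 enrolled, about 1275 evaluable at 15% dropout, gives about 76% power for 25% versus 15%.*
- **Keep 80% and state the dropout it allows.** This is about 10% if the chain stays at 514 × 2.63 = 1351, or about 6% once 514 is corrected to 534 (534 × 2.63 = 1404). The 10% figure must not be combined with the corrected 534.
- **If expected loss for the 7-day delirium assessment is below 15%,** state that rate, base the primary calculation on it, and keep any higher rate for the follow-up outcomes.

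In each case, correct 514 to 534 or name the method that gives 514. Leave 2.63 in place, but state the cluster-period size and number of baseline periods behind it so that it can be checked.

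The cost is wording only: no extra patients and no change to design or analysis. The downside is a slightly less favourable stated power, or a tighter stated dropout limit.

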## Methods

### Design

We have designed a cross-sectoral longitudinal study that aims to include 1500 patients undergoing elective surgery. The study employs a stepped-wedge design with cluster randomization of five medical centers. The study will have seven periods, each lasting 12 weeks (see Fig. 1). The study will evaluate an all-encompassing “best practice” multimodal intervention for preventing delirium and POCD that includes six consecutive measurement points: preadmission, preoperative, and postoperative including daily delirium screening for 7 days after surgery and 2, 6, and 12 months after surgery. We aim to show that: the cross-sectoral multimodal and multidisciplinary intervention reduces the delirium rate by at least 40% compared with treatment as usual; the cross-sectoral multimodal and multidisciplinary intervention reduces the rate of postoperative cognitive decline by at least 20% compared with treatment as usual; and the cross-sectoral intervention, including the team training and the modules for nonpharmacological prevention, is cost-effective and therefore the improvement in quality of life imposes no additional costs because the care needs of the patients and caregivers are lower than with the standard treatment.

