#### Recruitment

The study takes place in Germany in the state of Baden-Württemberg. The study will be performed in university hospitals in Tübingen, Freiburg, and Ulm, and in tertiary care hospitals (one in Stuttgart and two in Karlsruhe). In total, five medical centers (one per city) with 12 surgical departments (three in Stuttgart and Tübingen, and two at the other centers) are included. To balance the surgical subspecialties per center, recruitment is restricted to a maximum of 2/3 from one of the following surgical subspecialties: orthopedics, vessels and cardiac, or abdominal. We intend to maintain this ratio for every center and for every 12-week interval of the study.

Patient recruitment will be carried out by a medical specialist. Study staff, including doctors and scientists, will provide the necessary information and obtain the written informed consent from the patients, and whenever possible also from one relative (to assess the caregiver burden and the cognitive status of the patient).

The medical directors and the managers of anesthesia and nursing at the hospitals included in the study have provided a letter of intent expressing their interest in introducing and evaluating preventive procedures, and their willingness to recruit the necessary number of patients. Hence, the recruiting objective is realistic. However, if a department fails to meet its recruitment target (17 patients for the departments in Stuttgart and Tübingen, 25 patients for the others) during one period, concrete and binding measures will be taken to reach the planned number of patients. In this case, the center will commit either to increase the recruitment in its departments or to include another surgical department. If several departments do not reach their target, then the five recruitment blocks, each lasting 3 months, will be extended to 4 months, adding 33% more time to recruit. In this case, for the patients recruited during the last period of the project, the POCD assessments would be completed after 6 months instead of after 12 months.

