#### Randomization

Randomization will take place at the cluster level (*k* = 5 clusters) using a computer-generated sequence. Five months before starting the intervention in a given center, that center and the training team in Stuttgart will be informed about the allocation to prepare for the training and to form the intervention teams. Otherwise, randomization allocation will only be known to the consortium leader and the scientific staff at the University of Potsdam, who will implement the random sequence generation.

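### The stated minimum of 15 clusters does not follow from the protocol's own ratio, which gives 5.4 to 6, and the number of periods is given inconsistently as seven, five and, by implication, six

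*Protocol article*

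**What the plan says.** **Sample size.** The conventional calculation "results in a total of 514 patients with a 1:1 randomization". It is then adjusted for a stepped wedge with five crossing points, "with a maximum of 50 patients per cluster per period" and an intracluster correlation of 0.01. The correction factor is 2.63, which gives 1351 patients. After a dropout allowance the plan is for about 750 per arm, at most 1500 in all. The minimum cluster count is then obtained by dividing the patient total by "the product between the number of crossing points and the patients per cluster per period, and is 15".

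**Randomization.** "Randomization will take place at the cluster level", with k = 5. The Design section also names five medical centres as the randomised units. The Recruitment section lists 12 surgical departments within them.

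**Periods.** Design: "The study will have seven periods, each lasting 12 weeks". Recruitment, on what happens if several departments miss their targets: "then the five recruitment blocks, each lasting 3 months, will be extended to 4 months". Timelines: the study started in November 2017 and "the recruitment phase will last until April 2019". Table 1 dates the first enrolment 20 November 2017.

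**The concern.** All the inputs to the cluster ratio appear in the same paragraph as its result, and they do not produce that result. The figure also sits beside a design with five randomised clusters. A reader cannot tell whether the number is wrong, whether a different unit of clustering was meant, or whether the trial falls short of a requirement that it set itself.

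The number of periods is a basic parameter of a stepped wedge. With the number of centres and the patients per centre-period, it fixes the accrual capacity and enters the design factor. Two sections give two different counts, and the other stated figures point to a third. Whoever programs the analysis or checks the sample size has to guess which one applies.

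**Working it through.** **Inputs.** From Sample size: 514 patients unadjusted, five crossing points, at most 50 per cluster per period, intracluster correlation 0.01, factor 2.63, 1351 before dropout, 1500 planned, and 1079 for the secondary outcome. From Table 1: 1800 for the risk score. From Randomization: k = 5. From Recruitment: 12 departments, with targets of 17 (three departments each in Stuttgart and Tübingen) or 25 (two in each of the other three centres) per period.

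**1. What reproduces.** 514 × 2.63 = 1351.8, which is the protocol's 1351.

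**2. The cluster ratio.** Clusters = N / (crossing points × patients per cluster-period), with denominator 5 × 50 = 250.

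| N | N/250 |
|---|---|
| 514 | 2.06 |
| 1079 | 4.32 |
| 1351 | 5.40 |
| 1500 | 6.00 |
| 1800 | 7.20 |

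None comes near 15.

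**3. What 15 would require.** With five crossing points: 1351/(5×15) = 18.0 or 1500/(5×15) = 20 patients per cluster-period. That is about the size of a department, but it contradicts the stated 50, and there are only 12 departments.

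**4. What gives the five centres.** With six periods in the denominator: 1500/(6×50) = 5.0. With five crossing points the same ratio gives 6, one more than are randomised.

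**5. Number of periods.**
- Five crossing points plus one baseline period make six. At least one baseline period is needed, because the Intervention section compares against usual care in each centre before its randomised start.
- 1500/(5 centres × 50) = 6.
- From 20 November 2017, 72 weeks (six periods) end on 8 April 2019, inside the stated recruitment window. Five 12-week periods (60 weeks) end on 14 January 2019, and seven (84 weeks) on 1 July 2019.

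**6. Accrual under each count.** The department targets sum to 6×17 + 6×25 = 252 per period.

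| Periods | At 250 per period | At department targets (252) |
|---|---|---|
| 5 | 1250 | 1260 |
| 6 | 1500 | 1512 |
| 7 | 1750 | 1764 |

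Five blocks fall below 1351, and seven exceed the maximum of 1500.

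**7. Design factor for the six-period geometry.** I used the adjustment that the protocol names, with k = 5 steps, b = 1 baseline period, one measurement period per step, n = 50 and ρ = 0.01:

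[1 + ρ(kn + bn − 1)] / [1 + ρ(kn/2 + bn − 1)] × 3(1 − ρ) / [2(k − 1/k)]

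= (3.99/2.74) × (2.97/9.6) = 0.4505 per period.

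Times six periods this is 2.70, so 514 × 2.703 ≈ 1389 evaluable patients. Against 1351 that is 38 more, or 2.8%. At n = 40 the factor is 2.63, so the stated value fits a smaller cell than the stated maximum.

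**The case against.** The best defence is that 15 is a stray final figure. It feeds into none of 514, 2.63, 1351 or 1500. That is right, and it rules out several stronger readings that a reader might draw.

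- *The trial misses its own minimum by a factor of three.* This treats 15 as a genuine requirement, whereas the protocol's own inputs show it to be an error. Read literally, the ratio asks for six against five randomised, and that gap closes once periods replace crossing points.
- *The power claim fails.* It does not fail on this account. A standard linear mixed-model calculation for a stepped wedge (25% against 15%, five clusters, six periods, intracluster correlation 0.01, two-sided 5%, normal reference) gives 80% power at 1351 evaluable patients. Whether 1500 leaves enough patients after 15% dropout is a separate question. A small-sample reference for the test is commonly left to the analysis plan, which is not shown.
- *The period count swings the design factor widely.* With one baseline period kept, five, six and seven periods give 2.78, 2.70 and 2.68, about 1376 to 1426 patients. Wider ranges need zero or two baseline periods. Zero would leave the first centre without a control period, and two is not stated anywhere in the text.

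It is also fair to say that study periods and recruitment blocks need not be the same count, and that Fig. 1, to which the protocol refers for the numbers per period, is not shown here. A period without recruitment could reconcile seven with six. It could not reconcile five recruitment blocks with the six that the sample size and dates imply.

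**Conclusion.** The point stands as an error of arithmetic and consistency. The minimum of 15 clusters is wrong on the protocol's own inputs: the stated ratio gives 5.4 to 6, and five centres are randomised. The ratio itself matches the design only with six periods in the denominator. Seven periods and five recruitment blocks are not reconciled in the text, and the crossing points, the sample size and the dates agree on six.

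The effect on the sample size is small. At the stated 50 per cell the factor is 2.70 rather than 2.63, which adds about 38 evaluable patients. The larger practical effect lies in the accrual statement, where five blocks would hold about 1250 patients and seven about 1750.

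This rests on two assumptions: one baseline period, and 50 patients per centre-period as the working cell size, although the protocol calls 50 a maximum. That 15 came from a department-sized cluster is conjecture and is not needed for the conclusion.

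**What to change.** 1. In Sample size, replace 15 with the figure for the stated design, and define the ratio with periods in place of crossing points: 1500/(6×50) = 5 centres. Deleting the number alone is not enough, because the remaining formula would still return 5.4 to 6.
2. State one geometry and use it in Design, Sample size and Recruitment: five centres, six recruiting periods of 12 weeks, 50 patients per centre-period, 1500 in total. If there is a seventh period, say what it is for. Bring the five 3-month blocks into line with this.
3. Recompute the design factor from that geometry. At 50 per cell it is 2.70, or about 1389 evaluable patients. If 2.63 is kept, state the cell size that yields it (about 40).

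The cost is a wording correction in three sections and one recalculation. The randomisation, the number of centres and the cap of 1500 do not have to change on this account.

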#### Recruitment

The study takes place in Germany in the state of Baden-Württemberg. The study will be performed in university hospitals in Tübingen, Freiburg, and Ulm, and in tertiary care hospitals (one in Stuttgart and two in Karlsruhe). In total, five medical centers (one per city) with 12 surgical departments (three in Stuttgart and Tübingen, and two at the other centers) are included. To balance the surgical subspecialties per center, recruitment is restricted to a maximum of 2/3 from one of the following surgical subspecialties: orthopedics, vessels and cardiac, or abdominal. We intend to maintain this ratio for every center and for every 12-week interval of the study.

Patient recruitment will be carried out by a medical specialist. Study staff, including doctors and scientists, will provide the necessary information and obtain the written informed consent from the patients, and whenever possible also from one relative (to assess the caregiver burden and the cognitive status of the patient).

The medical directors and the managers of anesthesia and nursing at the hospitals included in the study have provided a letter of intent expressing their interest in introducing and evaluating preventive procedures, and their willingness to recruit the necessary number of patients. Hence, the recruiting objective is realistic. However, if a department fails to meet its recruitment target (17 patients for the departments in Stuttgart and Tübingen, 25 patients for the others) during one period, concrete and binding measures will be taken to reach the planned number of patients. In this case, the center will commit either to increase the recruitment in its departments or to include another surgical department. If several departments do not reach their target, then the five recruitment blocks, each lasting 3 months, will be extended to 4 months, adding 33% more time to recruit. In this case, for the patients recruited during the last period of the project, the POCD assessments would be completed after 6 months instead of after 12 months.

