#### Exclusion criteria

Patients undergoing emergency surgery procedures, patients unable to consent due to insufficient mastery of the German language or with newly discovered severe dementia (red flag: Mini Mental State Examination (MMSE) < 15, Montreal Cognitive Assessment (MoCA) < 8) without a substitute decision-maker, patients with a poor clinical prognosis (expected survival of less than 15 months), and patients who have a long driving distance to the study site (> 120 km) are to be excluded from the trial.

The recruitment procedure is described in Fig. 2. Patients who are not able to consent may also be recruited if the legal guardian consents to the patient’s study participation, given that such patients are especially at risk of developing delirium and POCD after surgery [10], and they could eminently benefit from the intervention.

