#### Statistical analysis

For the primary outcome, logistic regression analyses with cluster adjustment are planned.

For the secondary outcomes, the changes in the medication and the care burden of the patients’ relatives, we plan analyses using mixed linear and logistic regression models, with fixed and random factors for estimating heterogeneity over clusters [68].

Subgroup analyses for specific patient groups (e.g., patients with cardiac surgery regarding cognitive status or patients with brief hospital stays/brief surgeries) are planned.

For planned validity assessments of postoperative delirium, the validity of the I-CAM-S and NuDESC vs the RASS will be evaluated as screening tools for postoperative delirium. Diagnostic test performance of the tools will be evaluated by receiver operating characteristics (ROC) analysis.

Missing data (due to nonadherence of a department or a particular patient) will be documented. We will apply mixed-effect models, which handle the missing data without using any imputation method. Mixed-effect models assume that the missing data are missing at random (MAR); that is, when the probability that an outcome is missing is related to some other fully observable variable in the model, but not to the variable with the missing value itself [69].

Regarding the health-economic evaluation, a micro-costing analysis will be carried out using data from the clinical administration of two hospitals (Tübingen and Stuttgart). Moreover, for the patients insured by a specific health insurance (AOK Baden-Württemberg) who consent, the health and care insurance costs of the 12 months before and after surgery will be calculated using a difference-in-difference approach [70]. In this case, the target parameter is the cost per avoided POCD. The cost-effectiveness of the intervention will be calculated comparing the costs of the intervention group and the control group. In addition, quality-adjusted life years (QALYs) will then be calculated using data from the EQ-5D-5 L form about health-related quality of life, and applied for calculating the incremental cost-effectiveness. When possible, subgroup analyses will be carried out, for example, by age or gender, to determine whether cost-effectiveness is different in the corresponding groups. Sensitivity analyses will also be performed. The evaluation will be carried out following the recommendations of the “Good practice secondary data analysis” (GPS).

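### Patients are enrolled individually at centres whose current arm is evident, and the stated primary model does not remove a resulting shift in baseline delirium risk between phases

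*Protocol article*

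**What the plan says.** - **Randomisation:** the five centres are the randomised units. A centre and the training team are told its allocation five months before its intervention starts.
- **Intervention:** ward and medical staff are trained in the 4 to 6 weeks before the start. Signs, whiteboards and clocks then go up, and a dedicated team visits patients daily.
- **Recruitment:** "Patient recruitment will be carried out by a medical specialist", and study staff obtain written consent patient by patient. Department targets per period are "17 patients for the departments in Stuttgart and Tübingen, 25 patients for the others". No single subspecialty may supply more than two thirds of a centre's patients, a ratio to be kept in each 12-week interval.
- **Timelines:** preadmission screening takes place no more than three weeks before admission.
- **Outcome assessment:** the outcome assessors are blinded. Nothing comparable is stated for those who recruit.
- **Statistical analysis:** "For the primary outcome, logistic regression analyses with cluster adjustment are planned". No baseline risk factor is named for this model.
- **Background:** delirium incidence is said to depend on age, dementia, comorbidity and frailty, among other factors.

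**The concern.** Randomising centres balances centre-level features, and with five centres only roughly. It does not make the patients enrolled before and after a switch comparable when each is chosen and consented individually at a place where the arm is evident. Recruiters may approach different patients, and patients or relatives may respond differently once a prevention programme is on offer.

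Every centre contributes both phases, so such a shift lies within centres, and adjustment for cluster leaves it in the treatment estimate. Depending on its direction, it could produce part of the 40% reduction the trial aims to show, or hide part of a real one.

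**Working it through.** **1. The plan's own figure.** Inputs from Sample size: 25% against 15%, power 0.80, α 5% (sidedness not stated; two-sided assumed). The pooled normal formula gives (1.96·√(2·0.20·0.80) + 0.8416·√(0.25·0.75 + 0.15·0.85))² / 0.10² = 250 per arm, or 500 in total. The plan says its Fisher calculation "results in a total of 514 patients with a 1:1 randomization", which is within 3%. The design factor gives 514 × 2.63 = 1351.8, stated as 1351. These figures serve as the base and are not disputed here.

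**2. Effective size.** 1351 / 2 / 2.63 = 257 per arm. The standard error at 25% against 15% is √((0.1875 + 0.1275)/257) = 0.035, and power is Φ(0.10/0.035 − 1.96) = 0.815.

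**3. Risk by cognitive status.** Ethics expects about 40% of patients examined at preadmission to be cognitively impaired. The odds ratio of delirium for impairment is an assumption: 2, 3 or 4. Solving 0.6·p0 + 0.4·p1 = 0.25 gives p0/p1 of 19.7%/32.9%, 16.7%/37.5% and 14.6%/40.6%.

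**4. No true effect, fewer impaired patients in the intervention phase.** The shift d in the impaired share is also an assumption: 5, 10 or 20 points. The false reduction is b = d·(p1 − p0). Type I error is 1 − Φ(1.96 − b/SE) + Φ(−1.96 − b/SE), with SE from 257 per arm at 25% and 25% − b.

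| Odds ratio | d = 5 points | d = 10 points | d = 20 points |
|---|---|---|---|
| 2 | b 0.7 points; 5% | b 1.3 points; 6% | b 2.6 points; 11% |
| 3 | b 1.0 points; 6% | b 2.1 points; 9% | b 4.2 points; 20% |
| 4 | b 1.3 points; 6% | b 2.6 points; 11% | b 5.2 points; 29% |

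At odds ratio 3 and 10 points, b is about a fifth of the planned 10 point difference.

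**5. True effect as planned, more impaired patients in the intervention phase.** Solving step 3 at 15% with odds ratio 3 gives 9.3% and 23.5%. A 10 point shift raises the intervention rate to 15% + 0.10 × 14.2 points = 16.4%. The apparent relative reduction falls from 40% to 34%, and power from 81% to 67% (73% at odds ratio 2, 64% at odds ratio 4).

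**6. Which model removes it.** A simulation used 5 centres × 6 recruiting periods × 50 patients = 1500, 750 per arm, with no true effect, no time trend and no between-centre variation (1500 runs). Assumed risks were 40% and 15%, an odds ratio of 3.8, which average to 25% at 40% impaired.

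| Model | d = 5: OR, type I error | d = 10 | d = 20 |
|---|---|---|---|
| Cluster | 0.93, 8.7% | 0.88, 16.9% | 0.77, 49.5% |
| Cluster + period | 0.94, 6.0% | 0.87, 9.7% | 0.77, 23.3% |
| Cluster + baseline impairment | 1.00, 5.5% | 1.00, 4.9% | 1.00, 4.6% |

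The cluster-only error rates exceed those in step 4 because the simulation uses all 1500 patients without the design factor, so the same bias meets a smaller standard error. A period term does not remove the bias. The baseline covariate does, in the ideal case where it is measured perfectly and is the only thing that shifts.

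**The case against.** Several stronger readings are tempting, and the document does not support them.

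- **That the final model will adjust for cluster and nothing else.** The protocol gives a one-line statement, does not exclude covariates, and may be extended in an analysis plan that is not shown. This stands. The point concerns the model as stated, and it is a recommendation to state a better one.
- **That recruiters pick from a surplus until a quota is full.** The figures 17 and 25 are targets with remedies for falling short. They do add up to about 50 per centre and period (3 × 17 = 51, 2 × 25 = 50), which Sample size treats as a maximum. But the number of eligible patients is not given, so room to choose is not established.
- **That the protocol supplies a motive for selective invitation.** The phrase "they could eminently benefit from the intervention" explains why patients unable to consent are eligible through a guardian. It applies in both phases.
- **That invitation is not consecutive.** The text refers to Fig. 2 for the recruitment procedure, and that figure was not available for this review. Nothing can be concluded from the text alone.
- **That recruiters certainly know the arm.** This is inferred from the disclosure to the centre, the training, the visible ward changes and the absence of stated recruiter blinding. Assessor blinding does not bear on it.

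The subspecialty cap is a real safeguard for surgery type. It still lets one subspecialty vary from none to two thirds, and it does not address age, cognition or frailty.

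**Conclusion.** The concern holds as a weakness of the stated primary model and should be corrected; selection has not been shown to occur. Individual enrolment where the arm is evident leaves room for a within-centre shift in risk, and cluster adjustment alone would pass it into the treatment effect.

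The size rests on two assumptions that the document does not supply: the odds ratio (2 to 4) and the shift in impaired share (5 to 20 points). At the low end the effect is negligible (0.7 points, type I error about 5%). At the high end it is serious (5.2 points, about 29%). The direction is unknown, so both a false benefit and a masked one are possible.

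**What to change.** In Statistical analysis, state the primary model as logistic regression with cluster adjustment plus prespecified baseline covariates: age, MoCA, comorbidity index, Clinical Frailty Scale and type of surgery. Report the model without them as a sensitivity analysis.

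No new data should be needed. The baseline list names age, the comorbidity index and the frailty scale, and surgery type is needed for eligibility and the cap. MoCA appears in the eligibility criteria and the test battery but not in the text's baseline list, so confirm that it is taken before surgery in all patients. The costs are small: the odds ratio becomes conditional on the covariates, and a rule is needed for missing baseline values. Adjustment removes measured risk only.

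Secondary, and only if Fig. 2 does not already require it: state in Recruitment that eligible patients on the elective lists are invited consecutively. This costs recruiters some freedom.
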